### Participant Timeline

Study flow is depicted in figure 1. Participants will be tested at three time points (baseline (Day 1), endpoint (Day 5), and follow-up (Week 5)). Baseline testing will be conducted prior to the commencement of the intervention (Day 1). Participants will then be randomised into either the active or sham group. The iTBS intervention will be delivered over Days 1–5. Endpoint testing will be conducted at the conclusion of the intervention period (Day 5). Follow-up testing will be conducted 4 weeks following completion of the intervention (Week 5).

**Figure 1 F1:**
[figure not shown]
Study flow diagram. Participants will receive either active or sham rTMS treatment. Participants will be tested at three time points (baseline (Day 1), endpoint (Day 5), and follow-up (Week 5)). FSH, follicle-stimulating hormone; rTMS, repetitive transcranial magnetic stimulation

### Sample Size Determination

An exploratory sample size of 60 participants has been chosen to maximise feasibility and recruitment potential and characterise the potential mechanisms of iTBS in this pilot clinical trial. This sample size was calculated using the following calculator for binary sample sizes: https://www.johndcook.com/binary_sample_size.html. The calculator is based on the rule of thumb which assumes significance α=0.05 and type II error β=0.20 (80% power). We are assuming a potential dropout rate of 20% based on previous clinical trial experience,^24^ which requires an additional 12 participants (72 total).

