### Outcomes

All outcomes were assessed at three time points and full details of the outcome measures are outlined in table 1. As this is a pilot clinical trial, primary outcomes are mechanistic and include cortical activity, assessed via electroencephalography (EEG). Paired-pulse TMS will be used to investigate activity within intracortical circuits as a co-primary outcome. Intracortical inhibition will be measured via short-interval intracortical inhibition (SICI) and long-interval intracortical inhibition (LICI).

**Table 1 T1:** Schedule of Activities

Activity	Online Screening	Phone Screening	Baseline	Endpoint	Follow-Up
Inclusion and Exclusion Criteria	X	X			
FSH Pathology		X			
TMS Adult Safety Screen Questionnaire		X			
Telephone Montreal Cognitive Assessment		X			
EEG Measures			X	X	X
TMS Measures			X	X	X
Heart Rate Variability			X	X	X
Skin Conductance			X	X	X
Saliva Collection			X	X	X
Urine Collection			X	X	X
Memory and Cognitive Confidence Scale			X	X	X
Rey Auditory Verbal Learning Test			X	X	X
D-KEFS Verbal Fluency			X	X	X
Symbol Digit Modality Test			X	X	X
Paced Serial Addition Test			X	X	X
Conners Continuous Performance Test-3			X	X	X
Visual Analogue Scale to Evaluate Fatigue Severity			X	X	X
Patient Health Questionnaire-9		X	X	X	X
General Anxiety Disorder-7			X	X	X
Pittsburgh Sleep Quality Index			X	X	X
Menopause-Specific Quality of Life			X	X	X

D-KEFS, Delis-Kaplan Executive Function System; EEG, Electroencephalogram; FSH, Follicle Stimulating Hormone; TMS, Transcranial Magnetic Stimulation.

Secondary outcomes include changes in subjective cognitive complaints and objective changes in verbal memory, verbal learning, verbal fluency, psychomotor processing speed, working memory, and sustained attention and vigilance. The clinical trial will also assess the effects of an rTMS intervention on the psychological symptom profile as secondary outcomes, including depressive mood, anxiety, sleep quality, and quality of life.

Tertiary outcomes include changes in autonomic function, which will be assessed via skin conductance and heart rate variability (HRV). Changes in inflammatory and energetic markers and neuroactive metabolites will be measured via saliva and/or urine analysis.

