### Allocation

Double-blinded randomisation will be facilitated using REDCap, allowing for both concealment and randomisation. A randomisation schedule will be automatically generated by REDCap. Participants will be randomly allocated to receive rTMS or sham at a 2:1 ratio using randomly permutated blocks of 6. The trial will be double-blinded, meaning that the participants and investigator will be blinded to treatment allocation.

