## DISCUSSION

This randomised, sham-controlled, double-blinded pilot trial will explore the neurophysiological, cognitive and mood effects of non-invasive brain stimulation during the late menopause transition. Building on prior research, it aims to address the evidence-practice gap in managing cognitive and mood symptoms via non-pharmacological methods.

As the first study of its kind, an exploratory sample size was selected based on previous mechanistic studies stimulating the DLPFC in healthy individuals, as well as rTMS/iTBS pilot trials reporting cognitive improvements in clinical populations (sample sizes typically 10–30). While efficacy conclusions are limited by the pilot design, the sample size allows for subgroup analyses of mechanistic outcomes. Mechanistic changes were prioritised as primary outcomes due to the exploratory nature of the study and the need to assess protocol feasibility for future efficacy trials. Results will also inform effect size estimates for adequately powered future studies.

Findings from this pilot clinical trial have the potential to advance our understanding of the underlying mechanisms that affect cognition and mood in menopause and offer the potential for new non-invasive treatments to mitigate symptoms. The successful implementation of this pilot trial could inform future trials and offer a scalable intervention to improve cognition and mood in females experiencing the late menopause transition.

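### The sample size of 60 is justified by a calculator for binary outcomes at 80% power, but the primary and co-primary outcomes are continuous, so the 80% applies to none of them

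*Protocol article*

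**What the plan says.** **Sample Size Determination** gives two bases for the size. It opens with feasibility: "An exploratory sample size of 60 participants has been chosen to maximise feasibility and recruitment potential". It then says "This sample size was calculated using the following calculator for binary sample sizes", and adds "The calculator is based on the rule of thumb which assumes significance α=0.05" with β=0.20, that is, 80% power. No endpoint is named. An assumed 20% dropout adds 12 participants, for 72 in total.

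**Outcomes** says that the "primary outcomes are mechanistic and include cortical activity, assessed via electroencephalography (EEG"). It makes paired-pulse TMS, measured as SICI and LICI, the co-primary outcome.

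**Allocation**: "Participants will be randomly allocated to receive rTMS or sham at a 2:1 ratio using randomly permutated blocks of 6".

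**Statistical Methods** analyses continuous variables by t-test and repeated measures by generalised linear models. It defines no responder endpoint for EEG, SICI or LICI. It specifies two-tailed t-tests in its first paragraph and one-tailed testing throughout at the end of its second.

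**Discussion** gives a third basis for the size, namely earlier mechanistic studies and pilot trials, and adds that "the sample size allows for subgroup analyses of mechanistic outcomes".

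**The concern.** A sample-size calculation for two proportions has power for a stated difference between two proportions. The primary outcomes here are measured on continuous scales, where power depends on the difference relative to the SD. The α and β quoted with the calculator therefore do not carry over to EEG, SICI or LICI. This is an error in what the article states, and more detail elsewhere would not make a binary calculation suit these outcomes.

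The size also has three stated origins (feasibility, a power calculation, earlier studies), and the reader cannot tell which governs. At stake is how the results are read. A flat EEG or SICI result might be credited with 80% power that was never worked out for it. The Discussion also intends the results to inform effect sizes for later trials, so the precision of those estimates should be stated on the right scale.

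**Working it through.** **1. Can the 60 be reproduced?** Inputs given: α=0.05, power 80%, binary outcome. The two proportions are not given, so it cannot. Many unstated pairs come close. With 1:1 allocation and a two-sided test without continuity correction, 0.20 v 0.55 needs 29 per arm and 0.30 v 0.65 needs 31. With the usual rule of thumb, n per arm = 16·p̄(1−p̄)/d²:
- 0.05 v 0.35: 16 × 0.20 × 0.80 / 0.30² = 28.4, so 29 per arm.
- 0.15 v 0.50: 16 × 0.325 × 0.675 / 0.35² = 28.7, so 29 per arm.

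The implied difference is about 30 to 40 percentage points, and the article ties none of these pairs to an outcome.

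**2. Numbers available for analysis.** The 72 is 60 × 1.20. At 2:1, 60 completers are 40 active and 20 sham. With the article's own 20% loss, 72 × 0.80 = 57.6, or about 38:19. Both cases are carried forward.

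**3. Detectable difference on a continuous outcome.** One unadjusted between-group comparison, in SD units. SE = √(1/n₁ + 1/n₂).
- 40:20: √(1/40 + 1/20) = 0.274
- 38:19: √(1/38 + 1/19) = 0.281

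Normal approximation at 40:20, two-sided 0.05: (1.960 + 0.842) × 0.274 = 0.77 SD. The noncentral t gives slightly more:

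| Completers | 80% power, two-sided 0.05 | 80% power, one-sided 0.05 | 95% CI half-width (t × SE) |
|---|---|---|---|
| 40:20 | 0.78 SD | 0.69 SD | 2.002 × 0.274 = 0.55 SD |
| 38:19 | 0.80 SD | 0.71 SD | 2.004 × 0.281 = 0.56 SD |

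Both sidedness columns are shown because Statistical Methods contradicts itself on this.

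**4. Effect of baseline adjustment.** Adjusting for a baseline correlated r with the outcome multiplies the SE by √(1−r²). The article gives no r, so 0.5 to 0.7 is assumed. Two-sided:
- r = 0.5 (factor 0.866): 0.780 × 0.866 = 0.68 SD at 40:20; 0.801 × 0.866 = 0.69 SD at 38:19.
- r = 0.7 (factor 0.714): 0.780 × 0.714 = 0.56 SD at 40:20; 0.801 × 0.714 = 0.57 SD at 38:19.

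**5. Effect of 2:1 allocation.** The article does not say which ratio the calculator assumed. If it was 1:1, the effect with 80% power at 30:30 (0.723 SD, normal approximation) has 75% power at 40:20. The cost is about 5 points.

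**6. Subgroups.** No subgroup is named. An assumed half-and-half split of 40:20 leaves 20:10. The two-sided difference detectable with 80% power within that half is 1.12 SD (noncentral t, unadjusted).

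**The case against.** The best defence is that the article attaches the 80% to the tool and never says that the trial has 80% power for EEG, SICI or LICI. It calls the size exploratory, lists the small sample as a limitation, says efficacy conclusions are limited, and looks ahead to adequately powered later studies. That framing stands, and it lowers the severity. It does not remove the error, because the text still says that 60 was calculated by a method that fits none of the primary outcomes.

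Four stronger readings are tempting, and the document does not support them.
- *The trial is underpowered.* No target effect is stated, so 60 cannot be called too small. Detectable differences run from about 0.56 to 0.80 SD depending on sidedness, dropout and baseline adjustment.
- *The missing proportions are a defect in themselves.* A journal article may leave such inputs to the full protocol, which is not shown. The wrong outcome type is the stated error.
- *The 2:1 ratio invalidates the calculation.* That the calculator assumed 1:1 is an inference, and the cost would be modest.
- *The article claims power for subgroups.* It says only that the size allows subgroup analyses. The 1.12 SD figure rests on an assumed split.

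The logistic regression in Statistical Methods does imply a binary variable, but it relates biomarkers to changes in cognition and mood. It is neither a primary outcome nor a comparison of arms, and the sample size is not linked to it.

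**Conclusion.** The stated basis for the sample size is wrong as written: a binary calculation at 80% power is offered for a trial whose primary and co-primary outcomes are continuous. The table in the working gives what the design offers on such an outcome. Those figures assume one unadjusted comparison with no multiplicity allowance; the adjusted figures also assume the baseline correlation. They describe the design and do not condemn its size. The subgroup sentence is a secondary matter of wording. This should be fixed, but it is a correction of the text in a pilot that already calls its size exploratory, and it affects no participant, procedure or analysis.

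**What to change.** Keep N at 72 randomised.
- In Sample Size Determination, withdraw the binary calculation and the 80% figure as the justification, and say openly that they are withdrawn. State that the size is exploratory and feasibility-based, and make the Discussion's account agree.
- Give the expected precision or the detectable standardised difference for the continuous co-primary outcomes at about 38:19 to 40:20. Name the measure to which it applies and say whether it is before or after baseline adjustment. Unadjusted and two-sided, that is a 95% CI half-width of 0.55 to 0.56 SD and a detectable difference of 0.78 to 0.80 SD.
- Resolve the one-tailed/two-tailed conflict in Statistical Methods first, then state the sidedness beside these figures.
- Reword the Discussion's subgroup sentence so that any subgroup results are descriptive and reported with confidence intervals.

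The cost is wording only. The downside is that the stated justification looks less favourable than a claim of 80% power.

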**Methods and analysis:**

The aim of this 5-week randomised, sham-controlled, double-blinded pilot clinical trial (n=72) is to assess the underlying mechanisms of action of iTBS in females in the late menopause transition and the relationship with cognition and mood. Data will be analysed using Stata^TM^. Normality checks will guide the choice between parametric and non-parametric tests. Generalised linear models will assess within-subject and between-subject effects across timepoints, with additional regression analyses exploring associations between biomarkers, cognition and mood. Effect sizes, CIs and relevant test statistics will be reported, with significance set at p<0.05.

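### The 20% dropout allowance is taken on 60 rather than on the number enrolled, so 72 participants yield about 57 to 58 completers, not 60

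*Protocol article*

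**What the plan says.** All the figures stand in the protocol article.

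- **Size before dropout** (Sample Size Determination): "An exploratory sample size of 60 participants has been chosen to maximise feasibility and recruitment potential". The section adds that "This sample size was calculated using the following calculator for binary sample sizes", under a rule of thumb that "assumes significance α=0.05 and type II error β=0.20 (80% power").
- **Dropout** (same section): "We are assuming a potential dropout rate of 20% based on previous clinical trial experience".
- **Allowance** (same section): "which requires an additional 12 participants (72 total").
- **Enrolled total** (Abstract, Methods and analysis): "double-blinded pilot clinical trial (n=72").
- **Allocation** (Allocation section): participants are "randomly allocated to receive rTMS or sham at a 2:1 ratio using randomly permutated blocks of 6".

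The article does not define the dropout rate relative to the 60, does not accept fewer than 60 completers, and gives no completer target per arm.

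**The concern.** The 12 extra participants have one purpose: to leave 60 after the assumed loss. A dropout rate is a fraction of those who enter the trial. Here it has been applied to those meant to remain, which makes the allowance too small. The rate and the total therefore do not fit together: at 20% loss the enrolled 72 do not leave 60.

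What is at stake is modest. A reader will take 60 as the expected evaluable number, and it is not the number that follows from the plan's own assumption. Any power or precision figure built on 60 would be slightly optimistic. The retention needed to reach 60 is also stricter than the text implies, which is worth stating correctly in a single-site pilot meant to support a feasibility assessment.

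**Working it through.** **Inputs.** Size before dropout n = 60, dropout d = 0.20 and enrolled total N = 72 (Sample Size Determination; N also in the Abstract). Allocation 2:1 in blocks of 6 (Allocation).

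**1. Reproduce the plan's figure.** n × (1 + d) = 60 × 1.20 = 72, an addition of 0.20 × 60 = 12. This matches the stated total exactly.

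**2. Completers expected from 72.** N × (1 − d) = 72 × 0.80 = 57.6, that is 57 or 58. The shortfall against 60 is 2.4.

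**3. By arm.** At 2:1, 72 splits into 48 active and 24 sham (12 full blocks of 6).
- Active: 48 × 0.80 = 38.4
- Sham: 24 × 0.80 = 19.2

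**4. Enrolment that would keep 60.** n / (1 − d) = 60 / 0.80 = 75 (50:25), which is 15 extra rather than 12. Check: 75 × 0.80 = 60. Since 75 / 6 = 12.5, whole blocks would mean 78, with 78 × 0.80 = 62.4 expected completers.

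**5. Dropout that 72 can absorb.** (72 − 60) / 72 = 12 / 72 = 16.7%.

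**6. Chance of reaching 60.** Assuming each participant drops out independently with probability 0.20, completers are binomial. P(at least 60) is 0.30 with 72 enrolled and 0.57 with 75.

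**7. Size of the effect (reviewer's illustration; the article states no effect size or SD).** Assume a two-sided two-sample t-test on a mean, alpha 0.05, power 80%.
- 40 active and 20 sham (60 split 2:1): detectable difference 0.780 SD
- 38 active and 19 sham: detectable difference 0.801 SD

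The change is about 0.02 SD. Put as power, using the normal approximation: if 60 gave exactly 80%, 57.6 would give about 78.4%.

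**The case against.** **The 60 is not a hard requirement.** The article calls it exploratory and chosen for feasibility. The Discussion ties it to earlier studies with samples of typically 10 to 30 and says that efficacy conclusions are limited. No event rates or effect size are given, so no stated effect becomes undetectable at 57 or 58. This stands, and it limits the weight of the point. It does not remove it: the same section says that the size was calculated with 80% power and that the dropout rate makes the extra participants necessary.

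**Sham completers below 20.** A reader might infer that the trial misses a minimum of 20 in the sham arm. The article sets no such minimum. The 40:20 split is inferred from 60 and the 2:1 ratio, and 19.2 is less than one participant below it.

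**Loss of detectable effect.** A reader might also treat 0.78 and 0.80 SD as the plan's own figures. They are not. The section cites a calculator for binary outcomes and contains no precision statement, and Statistical Methods mentions both two-tailed and one-tailed testing. The figures only show how small the change is.

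**Completers are not the same as analysable participants.** This is fair. Endpoint testing is on Day 5 and follow-up in Week 5, and the article does not say when the 20% is lost. Anyone lost after Day 5 still contributes baseline and endpoint data, so at 20% total loss 57.6 is a lower bound for the Day 5 comparison.

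**Conclusion.** The stated increment does not follow from the stated rate. At 20% dropout, 72 enrolled give about 57 to 58 completers (about 38 active and 19 sham); 60 would need 75 enrolled, or dropout of at most 16.7%. This is certain arithmetic on the article's own figures, provided that dropout means a fraction of those enrolled, and the article offers no other definition.

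The consequence is small: 2 to 3 completers, or about 0.02 SD in an illustration that rests on an assumed two-sided comparison of means. It would be wrong to conclude that the trial is made unviable or that more participants must be recruited. The point is a wrong figure that should be restated.

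**What to change.** Keep 72 and replace the dropout sentence with, for example: *72 randomised (48:24) yield about 57–58 completers (about 38:19) at 20% dropout; 60 completers are reached if dropout is at most 16.7%.* Base any power or precision figure on that number rather than on 60.

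The cost is one restated sentence and no extra participants. If the sponsor prefers to protect 60 completers, the alternative is to enrol 75 (3 more), or 78 (6 more) to fill whole blocks of 6.

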### Recruitment Strategy

The primary recruitment strategy will use targeted social media advertising on the Meta platform, including Instagram and Facebook. Alternative recruitment channels include the research team’s networks, not-for-profit organisations and advocacy groups, such as Australasian Menopause Society (AMS). Interested parties will be invited to complete an online screening questionnaire to assess their initial eligibility for participation.

### Allocation

Double-blinded randomisation will be facilitated using REDCap, allowing for both concealment and randomisation. A randomisation schedule will be automatically generated by REDCap. Participants will be randomly allocated to receive rTMS or sham at a 2:1 ratio using randomly permutated blocks of 6. The trial will be double-blinded, meaning that the participants and investigator will be blinded to treatment allocation.

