**ANZCTR registration number:**

ACTRN12625000030471, Australian New Zealand Clinical Trials Registry

STRENGTHS AND LIMITATIONS OF THIS STUDYRandomised, double-blinded, sham-controlled design minimises bias and enhances internal validity.Multimodal assessments (electroencephalogram, transcranial magnetic stimulation, cognition, mood and biomarkers) capture both mechanistic and clinical effects.Clearly defined late-menopause transition criteria ensure a well-characterised sample.A matched sham coil reproducing the sound and scalp sensations of active stimulation maintains blinding integrity.Single-site pilot design with a small sample limits generalisability but supports feasibility assessment.

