Box 1Inclusion and Exclusion CriteriaInclusion CriteriaFemales aged between 45 to 55 years who are undergoing the late menopausal transition stage according to the STRAW criteria as defined by: (a) amenorrhoea of 60 days or longer; (b) follicle-stimulating hormone (FSH) levels greater than 25 IU/L in a random blood draw and (c) self-reported vasomotor symptoms.Females experiencing self-reported subjective cognitive complaints relative to previously normal cognitive status.Willing to complete all study-related activities for the complete trial, including in-person assessments and remote follow-ups.Exclusion CriteriaIndividuals who have contraindications to TMS.Reproductive age females; females in the late reproductive stage or the early menopausal transition and postmenopausal females.Females who have been receiving MHT treatment for less than 3 months at the time of recruitment or plan to commence MHT treatment during the study duration.Individuals using neuroactive medications, including anticonvulsants, antidepressants and anxiolytics.A diagnosis of neurodegenerative, psychiatric affective, non-affective or neurological illness.Significant cognitive impairment as deemed by scoring 17 or less on the Telephone Montreal Cognitive Assessment (T-MoCA).Current episode of major depression as deemed by scoring 15 or greater according to the Patient Health Questionnaire-9 (PHQ-9).High dependence on medical care due to past or current medical conditions.Study physician discretion regarding medical status, appropriateness of participation or concern about intervention adherence.Individuals who are not willing to follow the study protocol, eg, are not able to attend face-to-face visits or those who plan to move out of the area within the treatment period.Individuals who are actively participating in another clinical trial(s).Individuals who are not proficient in reading and writing in English.

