Sham will be delivered using a dedicated sham coil that reproduces the audible clicks and superficial somatic sensations of active stimulation, without delivering magnetic pulses to the cortex. The set-up will be handled by a blinded laboratory technician, and active and sham groups will receive identical information and instructions.

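### A single published block size of 6 at one site leaves concealment dependent on coil blinding: if that fails, about 29% of allocations are known in advance

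*Protocol article*

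**What the plan says.** The Allocation section of the protocol article fixes both the ratio and the block size: "Participants will be randomly allocated to receive rTMS or sham at a 2:1 ratio using randomly permutated blocks of 6". One size is given, with no variation and no stratification factor. The same section says that REDCap generates the schedule and conceals it, and that participants and investigator are blinded.

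The strengths and limitations list describes a "Single-site pilot design with a small sample limits generalisability but supports feasibility assessment". On this text there is one running sequence.

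The Intervention section gives the sham arm its own device: "Sham will be delivered using a dedicated sham coil that reproduces the audible clicks and superficial somatic sensations of active stimulation". The sentence that follows on staffing is "The set-up will be handled by a blinded laboratory technician".

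The exclusion criteria in Box 1 include a judgement-based item: "Study physician discretion regarding medical status, appropriateness of participation or concern about intervention adherence". The Participant Timeline section places baseline testing before randomisation.

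**The concern.** REDCap can hide the list, but it cannot hide what follows by subtraction. When every block is known to contain four active and two sham places, the rest of the block is determined once both sham places, or all four active places, have been used. Anyone who can reconstruct the past allocations in the block then knows the next ones.

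The plausible source of that knowledge is the equipment. A dedicated sham coil has to be selected and mounted by someone at the site. The article says that a blinded technician does the set-up, but not how that person remains unaware of which coil is in use.

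What is at stake is the period before randomisation. Entry is partly discretionary, and the baseline measures include the primary EEG and the co-primary paired-pulse TMS outcomes. A known next allocation could influence whether or when someone is enrolled, or how baseline testing is handled. It would also mean that staff knew a participant's arm before the first session.

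**Working it through.** The article gives no predictability figure, so there is none to reproduce.

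**Inputs**
- Ratio 2:1 and block size 6 (Allocation): 4 active (A) and 2 sham (S) per block.
- 72 participants (Sample Size Determination): 72/6 = 12 blocks, so 48 active and 24 sham.
- One sequence (single site, no stratification stated).
- Assumption: the observer knows all earlier allocations in the current block and where it began.

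**Certain allocations with fixed blocks of 6.** There are C(6,2) = 15 equally likely orderings. An allocation is certain when only one arm remains in the block.

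| Place in block | Orderings in which it is certain | Chance |
|---|---|---|
| 1 | 0 of 15 | 0% |
| 2 | 0 of 15 | 0% |
| 3 | 1 of 15 | 6.7% |
| 4 | 3 of 15 | 20.0% |
| 5 | 7 of 15 | 46.7% |
| 6 | 15 of 15 | 100% |

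The sum is (1 + 3 + 7 + 15)/15 = 26/15 = 1.733 per block. The closed form agrees: 4/(2+1) + 2/(4+1) = 1.333 + 0.400 = 1.733, where the first term counts certain active places and the second certain sham places. As a share, 1.733/6 = 28.9%. Over the trial, 12 × 1.733 = 20.8 of 72.

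**Best-guess accuracy with fixed blocks of 6.** The observer always guesses the arm with more places left. The expected chance of being right at places 1 to 6 is 0.667, 0.667, 0.667, 0.733, 0.733 and 1. The mean is 4.467/6 = 74.4%. Always guessing active, with no knowledge of the past, gives 4/6 = 66.7%.

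**Varying block sizes.** These were simulated with 2,000 lists of 72, each size equally likely, and an observer who knows the set of sizes and all past allocations but not the size of the current block. As a check, the same simulation with fixed blocks of 6 gave 28.8% certain and 74.4% correct, in line with the exact values.

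| Block sizes | Certain | Best guess correct |
|---|---|---|
| 6 (exact) | 28.9% | 74.4% |
| 3 and 6 | 10.0% | 75.5% |
| 6 and 9 | 5.3% | 73.0% |
| 3, 6 and 9 | 3.9% | 73.7% |

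Of 72 allocations, 5.3% is about 4 and 3.9% about 3, against about 21 with fixed blocks of 6. Mixing sizes removes most of the certainties but hardly changes the average success of guessing.

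**The case against.** The strongest reply is that the article already closes the route. It names participants, investigator and technician as blinded, describes a sham coil that reproduces the sound and scalp sensation of active stimulation, and places concealment in REDCap. Nothing in it says that staff can tell the coils apart. How the technician is kept blinded is an operational detail that the full protocol may give. Equal-sized permuted blocks with a computer-held list are a standard method, and 72 is a whole number of blocks. All of this stands. It makes the 29% conditional.

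A second reply also stands in part. Anyone who can recognise the coil learns each participant's arm at the first session under any block scheme. The fixed size adds only advance knowledge, which matters between screening and randomisation.

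Three stronger readings are tempting, and the document supports none of them.
- A reader might infer that selection bias will result. No passage says that the study physician sees the coils or knows past allocations, and the schedule of activities places eligibility checks at the online and phone screening stages.
- A reader might take 29% as the share of participants who will be unblinded. It is the share that would be predictable if the stated blinding failed completely.
- A reader might conclude that later participants are themselves unblinded. At most, a staff member could infer their arm.

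What the reply does not remove is that the article publishes both ratio and block size, so concealment of the remaining places in a block relies entirely on a coil-blinding step that it leaves unexplained.

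**Conclusion.** The point holds as a conditional weakness of minor weight. The single published block size is a poor choice for a single-site trial with an arm-specific coil, because it leaves no second line of defence if the coil becomes known. In that event 1.73 of 6 allocations (28.9%, about 21 of 72) would be certain in advance, and overall guessing would improve from 66.7% to 74.4%.

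These figures rest on three assumptions: complete knowledge of earlier allocations in the block, knowledge of where the block began, and one unstratified sequence. With partial knowledge they would be smaller. The document does not show that any leak occurs, so the finding concerns how well concealment is protected and not bias in the results.

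**What to change.** In the Allocation section, for the part of the list not yet used and starting at a block boundary, replace the fixed size with randomly varying block sizes that are multiples of 3, so that 2:1 is kept. Either 6 and 9, or 3, 6 and 9, would serve. State that the list is prepared by someone without participant contact, is held and released through REDCap, and that block sizes are withheld from site staff. The sentence saying that REDCap generates the schedule automatically would need to be reworded to match.

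The cost is regenerating the unused list. If recruitment ends mid-block, the arm totals may depart from 48:24 by one or two. The article does not give recruitment status. If the list is already used up, what remains is to report who knew the block size and who handled the coils.

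The change limits advance knowledge only. It does nothing about recognition of the coil itself, so how the person setting up the dedicated coil stays blinded still needs to be stated separately.
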